## Abstract

**Background:**

Aging is associated with chronic low-grade inflammatory activity with an elevation of cytokine levels. An association between regular physical activity and reduction of blood levels of anti-inflammatory cytokines is demonstrated in the literature pointing to an anti-inflammatory effect related to exercise. However, there is no consensus regarding which type of exercise and which parameters are the most appropriate to influence inflammatory markers. Evidence indicates that the single nucleotide polymorphism (SNP) can influence the synthesis of those cytokines affecting their production.

**Methods/Design:**

The design of this study is a randomized controlled trial. The aim of this study is to investigate the interaction between the cytokine genes SNP and the effect of physical activity on older women. The main outcomes are: serum levels of sTNFR-1, sTNFR-2, interleukin (IL)-6, IL-10, measured by the ELISA method; genotyping of tumor necrosis factor- (TNF)-alpha (rs1800629), IL6 (rs1800795), IL10 (rs1800896) by the TaqMan Method (Applied Biosystems, Foster City, CA, USA); and physical performance assessed by Timed Up and Go and 10-Meter Walk Tests. Secondary outcomes include: Geriatric Depression Scale, Perceived Stress Scaleand aerobic capacity, assessed by the six-minute walk; and lower limb muscle strength, using an isokinetic dinamometer (Biodex Medical Systems, Inc., Shirley, NY,USA). Both exercise protocols will be performed three times a week for 10 weeks, 30 sessions in total.

**Discussion:**

Investigating the interaction between genetic factors and exercise effects of both protocols of exercise on the levels of inflammatory cytokine levels can contribute to guide clinical practice related to treatment and prevention of functional changes due to chronic inflammatory activity in older adults. This approach could develop new perspectives on preventive and treatment proposals in physical therapy and in the management of the older patient.

**Trial registration:**

(ReBEC) RBR9v9cwf

## Background

Aging is associated with a chronic low-grade inflammatory process characterized by a systemic elevation, from two to four times, of plasma levels of cytokines as interleukin (IL)-1, tumor necrosis factor alpha (TNF-α), IL-6, acute phase proteins, soluble TNF receptors (sTNFR) and IL-10, among others [1]. The balance between production and release of those cytokines has been related to the emergence or aggravation of chronic conditions related to aging, disability and increased mortality in olderadults[1,2]. High levels of cytokines are associated with a reduction of physical performance and muscle function [3-7]. The underlying mechanism by which these cytokines contribute to a functional deterioration in olderadults seems to be their catabolic effect, leading to a reduction in muscle mass and strength that are related to sarcopenia [1,8].

TNF-α is an early mediator of inflammation since it starts and coordinates the acute phase response and induces the production of a second wave of cytokine expression, such as IL-6, IL-8 and C-reactive protein [9]. It also stimulates the production of sTNFR that acts as its natural inhibitor; therefore, regulating its biological function. Since these receptors are more stable molecules than TNF-α in circulation, they are more reliable markers of plasma TNF-α levels, and hence of the inflammatory response [10]. A few authors argue that TNF-α is behind the age-related inflammatory changes [11,12], being associated with the development of insulin resistance and metabolic syndrome [13], and also with reduction of muscle mass and strength loss due to its catabolic action [14].

IL-6 is a cytokine that has both pro- and anti-inflammatory roles and is involved in controlling and coordinating inflammatory responses. It is produced by different cell types, which include the skeletal muscle cells [15]. On the other hand, IL-10 is an anti-inflammatory cytokine that is essential to inflammatory activity control and resolution that is triggered and sustained by other mediators [16]. The IL-10 inhibitory effect on IL-6 and TNF-α cytokines is well established in acute inflammatory processes [17], but not in chronic inflammation, such as we see during aging. The impact of physical exercises on their plasma levels is not known.

Differences seen in protein expression among people can occur as a result of functional genetic variations in the promoter area of these molecules gene [18]. The most common variations seen on human genomes are the single nucleotide polymorphism (SNP). Evidence points that SNPs, which are present in the genes of several molecules involved in inflammation, could affect their gene transcription and synthesis [18], modulating the inflammatory response severity. Some polymorphisms are associated with a greater production of inflammatory mediators. Thus, gene variations could explain in part the variability in the production of cytokines, and the greater liability of certain people to clinical conditions that are mediated by the elevation of these markers’ production, such as chronic conditions related to aging and longevity [19-21].

The expression of TNF-α, IL-6 and IL-10 is influenced by functional polymorphisms at their promoter areas. The polymorphisms in TNF-α (rs1800629), IL-6 (rs1800795) and IL-10 (rs1800896) have been associated with several acute and chronic diseases and with longevity as well [1,19,22]. For instance, Oberbach *et al.*[22] identified that changes in the IL-6 plasma levels in response to exercise were influenced by the -174 G/C polymorphism, suggesting that genetic factors related to cytokine production could be determinant to individual effects of the anti-inflammatory response promoted by exercise. However, literature presents contradictory results related to their activity and effects on plasma levels of these mediators, especially considering the older population. One possibility is that differences shown in the literature are due to interactions between lifestyle and gene factors, along with cultural and ethnic differences of the different studied samples.

Observational studies have pointed out that physically active people have lower concentrations of inflammatory cytokines, suggesting that regular exercise may alleviate the chronic inflammatory activity associated with aging [15,23,24]. Consistent evidence has demonstrated that physical activity induces an elevation of anti-inflammatory cytokine systemic levels [25-27], with the skeletal muscle tissue being indicated as an endocrine organ that produces and releases cytokines called miokines [15].

The production and release of IL-6 during physical activity seem to rely on factors such as type, intensity and duration of exercise [26]. Despite the possible benefits of physical exercise on chronic inflammatory process, information about the parameters of the ideal exercises for regulating cytokines have not been established [28-31], with research results being conflicting.

Therefore, the primary objective of this clinical trial is to investigate the existence of an interaction among TNF-α rs1800629, IL6 rs1800795, IL10 rs1800896 and gene polymorphisms with the effect of physical exercise in older women.

## Methods/Design

### Recruitment of participants

This study is a randomized controlled trial for which community-dwellingolder women will be recruited and randomly assigned to either one of the following physical activity protocol: muscle strengthening exercises (MSE) or aerobic exercises (AE). Participants will be recruited from the community through publicity in local newspapers and community centers for older persons. The study will be conducted at the Universidade Federal de Minas Gerais, Belo Horizonte, Brazil.

After the initial evaluation, participants will be randomized into either the MSE or AE group. Randomization will be performed by means of sealed brown envelopes without identification. The researcher responsible for the evaluations will be blinded to the participants’ group.

The study was approved by the Ethics Committee of Universidade Federal de Minas Gerais (ETIC 038/2010) and all volunteers will give their written informed consent to participate, according to the principles of the Helsinki Declaration (1964).

### Sample

#### Inclusion criteria

Community-dwellingolder women who are sedentary and aged 65 years or more will be included in the study. Sedentary older women are those who have not practiced any regular physical activity (that is, at least three times a week, 40 minutes minimum) in the last three months.

#### Exclusion criteria

Older people with cognitive impairment detectable by the Mini Mental State Examination [32], acute phase inflammatory disease, a history of cancer, current use of immunomodulatory medications, amputation or lower limb fracture in the last six months, presence of neurological sequelae or current participation in an alternative exercise program will be excluded from the study.

#### Baseline assessment

A standardized questionnaire will be applied by trained researchers to collect sample characteristics, socio-demographic data and information on the clinical condition of older adults.

#### Primary outcome measure

1. Plasma levels of TNF-α, sTNFR-1, sTNFR-2, IL-6, IL-10: 5 ml of blood will be withdrawn from the participants and immediately centrifuged at 1,500 rpm to obtain plasma. Aliquots will be removed in a laminar flow hood and stored at −80 °C. Plasma levels of cytokines will be determined by ELISA (enzyme-linked immunosorbent assay) method with high sensitivity kits (Quantikine®HS, R&D Systems, Minneapolis, MN, USA). According to the manufacturer the detection level of the method was 5 pg/ml for TNFRs, 0.15 pg/ml for IL-6 e 0.75 pg/ml for IL-10.

2. *Genotyping* – Blood samples will be obtained from all individuals in **ethylenediaminetetraacetic acid** (EDTA) anti-coagulant and genomic DNA will be extracted using a phenol-chloroform method from unfractionated whole blood, and stored at −20 °C. TaqMan genotyping assays will be obtained from Applied Biosystems, Inc. (Foster City, CA, USA). The assay identification code for each respective SNP is IL-10 (rs1800896), TNF (rs1800629). A customized assay will be used for the IL-6 SNP gene. All amplifications will be carried out in an ABI 7900HT thermal cycler (Applied Biosystems, Inc.) using TaqMan Genotyping Master Mix and following the manufacturer's recommended amplification conditions.

3. Physical Performance will be assessed by means of Timed Up and Go (TUG) [33] test and the 10-Meter Walk Test (10MWT) [34]. These tests will be used because they have demonstrated high reliability and are commonly used to assess function in older people. The TUG measures, in seconds, the time taken to stand up from a standard chair, walk a distance of three meters, turn, walk back to the chair and sit down. The TUG score demonstrates high inter-rater and intra-rater reliability (intraclass correlation coefficients (ICCs) 0.99 and 0.99 respectively) [35]. The 10MWT has good reliability (ICC = 0.78 e ICC = 0.93), and is a good marker for mobility and fall risk [36].

#### Secondary outcome measure

1. Muscle strength will be assessed using a Biodex® System 3 Pro isokinetic dynamometer (Biodex Medical Systems Inc., Shirley, NY,USA). This instrument has been accepted as the “gold standard” for assessment of muscular performance [37]. The muscle groups assessed will be the knee joint extensors and flexors of the dominant limb at angular speeds of 60° and 180° in concentric contractions, with 5 and 15 repetitions respectively, at intervals of 30 seconds between each velocity. All procedures will be performed according to the assessment protocol suggested by the manufacturer, such as positioning of the volunteer, calibration, correction for gravity, familiarization and strong verbal encouragement. Variables chosen for analysis are work normalized by body mass (%) at 60°, and Power at 180°.

2. Aerobic capacity, as measured by the 6-Minute Walk Test (6MWT). The 6MWT has been used in patients who have different disorders, such as neurological, cardiothoracic, infant or rheumatologic dysfunctions, and its correlation with maximum aerobic capacity is considered to be satisfactory [38,39]. Data related to systemic blood pressure, heart rate and subjective perception of effort using the Borg scale will be recorded.

3. Geriatric Depression Scale (GDS) is a screen for the presence of depression in older people. It comprises 15 individual questions; the cut-off-points will be 5/6 (non-case/case) [40,41].

4. The level of stress will be assessed by the 14-item Perceived Stress Scale validated for Brazilian older persons. This scale assesses three factors considered to be keys in the experience of stress: how the subject evaluates his life as unpredictable, uncontrollable and overloaded [42].

The salivary cortisol level will be measured as an objective measurement of stress [42]. The salivary cortisol level will be collected with cortisol specific Salivette tubes (Sarstedt.Salivette-swab). The dosage of the salivary levels will be performed using the ELISA method (*Salimetrics*).

### Intervention

The participants will be divided into two groups: strengthening exercises (SE) and aerobic exercises (AE) groups. Both groups will be submitted to a protocol lasting 10 weeks, 30 sessions in total, 3 times a week, under the direct supervision of a physical therapist.

### AE protocol

This protocol will consist of aerobic activities, including a 5-minute warm-up routine, 40 minutes of aerobic exercises – walking and free weight exercises for both upper and lower limbs, and a 5-minute cool down period, as recommended by the American College of Sports Medicine [43]. Heart rate will be maintained at 60% of age-predicted maximum heart rate during both warm-up and cool-down periods, and between 65% to 80% levels during the aerobic activity.

Blood pressure and heart rate will be measured at the beginning and at the end of every session. To ensure the safety of participants and to guarantee the proper training zone, each one of them will be monitored by a cardiac monitor.

### SE protocol

This program was based on a previous study (ISRCTN62824599) [44] developed by the Pain and Inflammation in Rehabilitation and Aging Studies Laboratory (Laboratório de Dor e Inflamação em Reabilitação e Estudos do Envelhecimento - LADIRE) research group.

The session will consist of a 10-minute walk, followed by stretching the rectus femoris, psoas, hamstrings and triceps surae muscles. Strengthening exercises will be performed for the following movements: hip flexion, abduction, adduction and extension; knee flexion and extension; mini-squat. The load, suitable for each participant, will be calculated by one repetition maximum (1RM) test. Participants will initiate the exercises at 50% of 1RM, adjusting the load after two weeks (seventh session) to 75% of 1RM. The RM will be recalculated for sessions 13 and 22, and the exercises will be performed at 75% of the newly established RM. Participants will be reassessed after 30 sessions.

### Sample size

Based on the multivariate linear regression analysis that will be performed in this study to explore the SNP influence on the effects of exercise on plasma levels of cytokines and onephysical performance, 140 older adults need to be included, considering the sample calculation of (10 x (K + 1), where K is the number of explanatory variables of the model. The explanatory variables are age, anthropometric measurements (Body Mass Index and Waist Circumference), physical activity level, presence of depression and stress levels (Perceived Stress Scale and salivary cortisol), TNF-α rs1800629 (AA + AG versus GG) , IL6 rs1800795 (GG versus CC + GC) , IL10 rs1800896 (GG versus AA + AG), genes polymorphisms.

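### The sample size of 140 does not follow from its own rule: the ten listed variables give 110, and the exercise group and SNP-by-group terms are not in the list

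*Protocol article*

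**What the plan says.** The Sample size section rests the number on the planned linear regression. Its stated purpose is "to explore the SNP influence on the effects of exercise on plasma levels of cytokines"; a second set of outcomes is physical performance. The rule and its result stand in one sentence: "140 older adults need to be included, considering the sample calculation of (10 x (K + 1"). K in this rule counts the model's explanatory variables.

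The section then names them. Seven are covariates: age, BMI, waist size, activity level, depression, the Perceived Stress Scale score and cortisol in saliva. The other three are the SNPs, each coded in two levels: "TNF-α rs1800629 (AA + AG versus GG) , IL6 rs1800795 (GG versus CC + GC) , IL10 rs1800896 (GG versus AA + AG").

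The aim, at the end of the Background, sets the SNPs against exercise: "the primary objective of this clinical trial is to investigate the existence of an interaction among TNF-α rs1800629, IL6 rs1800795, IL10 rs1800896". The Statistical analyses section says that the regression is to examine the interaction and the effect of the polymorphisms, with α at .05. It does not write the model out. The Sample size section gives no effect size, power or allowance for loss.

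**The concern.** The article prints the rule, its inputs and its result, and the result does not follow from the inputs. This is not a detail left to a fuller document: another document could close the gap only by changing one of the three printed statements.

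The list also contains neither the randomised group nor a product of group and SNP. A regression on the listed variables alone cannot estimate whether a genotype alters the difference between the two exercise programmes.

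The figure of 140 is the only planning number in the protocol, and it is presented as what the regression for the primary objective requires. A reader cannot tell which model it was sized for. A reader may also take it as assurance about the interaction, which a count of subjects per variable cannot give.

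**Working it through.** **Inputs (Sample size section).** The rule is N = 10 x (K + 1), and the stated N is 140.

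**The plan's figure.** 140 / 10 − 1 = 13, so 140 requires K = 13.

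**Count of the listed variables.**

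- Age, body mass index, waist circumference, physical activity level: 4
- Depression, Perceived Stress Scale, salivary cortisol: 3
- Three SNPs, each in two levels and so one term each: 3

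K = 10, so N = 10 x 11 = 110. The stated figure is not reproduced; the gap is 30 participants, or three terms. Counting grouped items as one variable widens it (K = 7 or 8, N = 80 or 90).

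**Other models under the same rule.** The plan writes out none of these.

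| Model | K | N |
|---|---|---|
| Ten listed + group | 11 | 120 |
| Ten listed + group + 3 SNP-by-group | 14 | 150 |
| The same + baseline outcome | 15 | 160 |
| Ten listed + group + 3 SNP-by-group + 3 SNP-by-SNP | 17 | 180 |
| One model per SNP: 7 covariates + SNP + group + product | 10 | 110 |
| One model per SNP + baseline outcome | 11 | 120 |
| Ten listed + 3 SNP-by-group, no group main effect | 13 | 140 |
| Ten listed + 3 SNP-by-SNP | 13 | 140 |
| Two indicator terms per SNP, no group | 13 | 140 |

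The last three rows reach 140. The first of them leaves out a main effect that its products need. The second does not test SNP by exercise. The third contradicts the printed two-level coding.

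**Unstated loss.** 110 / (1 − 0.20) = 138 and 120 / (1 − 0.15) = 142 come near 140. The section, however, attributes 140 to the rule itself and mentions no loss.

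**What 140 can detect for SNP by group.** The assumptions are mine: 70 per arm, 80% power, two-sided .05 (the plan does not state sidedness), no loss, no covariate adjustment, and the same carrier share p in both arms. The documents give no carrier shares.

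Within one arm, the variance of the genotype difference is SD² x [1/(70p) + 1/(70(1 − p))] = SD² / (70p(1 − p)). The interaction is the difference between the arms, so

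SE = SD x sqrt(2 / (70p(1 − p))), and the detectable effect is 2.80 x SE.

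| p | SE (SD) | Detectable (SD) |
|---|---|---|
| 50% | 0.338 | 0.95 |
| 35% | 0.354 | 0.99 |
| 20% | 0.423 | 1.18 |
| 15% | 0.473 | 1.33 |

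For comparison, the group main effect has SE = SD x sqrt(2/70) = 0.169 SD and is detectable at 2.80 x 0.169 = 0.47 SD.

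**The case against.** The strongest reply is that the model is nowhere written out, so no single N can be called the one the objective needs. That stands. A reader might infer that 140 is too small because the interaction model requires 150 to 160. The documents do not support this, since those figures hold only for one assumed joint model. The Statistical analyses section refers to the genotype of each polymorphism investigated, which is compatible with one model per SNP, and that gives 110 to 120.

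Both arms also exercise, so the effect of exercise could be read as change from before to after. The SNP coefficient on change would then carry the interaction without a group product. On that reading, and under the same assumptions, the detectable effect halves: SE = SD x sqrt(1 / (140p(1 − p))), giving 0.47 SD at 50% and 0.66 SD at 15%. The Abstract and the Discussion speak of the effects of both or different protocols, which favours a comparison of arms but does not settle the matter.

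It can also be said that K may simply be incompletely reported. Three SNP-by-SNP products bring the list to exactly 140, and the Discussion stresses the combined action of genotypes. That origin is possible but unconfirmed, and the printed list would still be wrong as the basis of the number.

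Finally, the practical gap is modest. For the listed variables 140 exceeds the rule's 110. For the joint models it gives 140/15 = 9.3 or 140/16 = 8.8 per (K + 1), against a target of 10. This is a good reason to keep 140, but not to leave its derivation as it stands. The section also makes no explicit power claim, so the point about precision is that none is offered, not that a stated power is false.

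**Conclusion.** The stated sample size does not follow from the stated rule and list: they give 110, and 140 needs three further terms that are not named. This rests on the Sample size section alone and on no assumption beyond one term per two-level SNP. The list's omission of the exercise group and the SNP-by-group terms is equally plain from the text.

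The figures beyond that are conditional. The 150 and 160 belong to one joint model, and the 110 to 120 to separate models per SNP. The detectable effects of 0.95 to 1.33 SD depend on a SNP-by-group estimand and on the assumptions set out with them. They show that the rule gives no assurance about the interaction. They do not show that the trial must enrol more participants.

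**What to change.** Keep 140 and rewrite the paragraph on its basis:

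- Put the exercise group and the SNP-by-group terms in the primary regression, and say whether there is one joint model or one model per SNP.
- List every term, including the baseline outcome if it is used. State K, the N that the rule then gives, and any allowance for loss, so that the figures agree with 140 or the difference is explained. With one joint model the rule gives 150 or 160, and the text should say that 140 falls slightly short of it. With separate models it gives 110 or 120, and any part of the remainder claimed as a loss allowance needs its own justification, because the documents give no attrition figure.
- Do not present 140 as sufficient for the interaction. State the detectable SNP-by-group effect at 140 over a range of carrier shares, with the assumptions.

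The cost is one rewritten paragraph and a less favourable stated precision. Dropping listed covariates to reduce K is optional and is not part of this correction.

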### Statistical analyses

Insight into the sample characterization will be provided using descriptive statistics, including measures of central tendency (mean and median) and variability (range and standard deviation). Violation of Hardy-Weinberg equilibrium will be tested by the chi-square test.

The Kolmogorov-Smirnov test will be used to verify the normal distribution of data. The comparison for between and within groups data will be analyzed using an analysis of variance (ANOVA). *Post hoc* testing will be undertaken with LSD tests.

The multivariate linear regression analysis will be performed to explore the interaction and the effect of polymorphisms on the variables: plasma levels of cytokines and physical performance, considering the genotype of each investigated.

Statistical analysis will be performed using the *Statistical Package for Social Sciences* (SPSS Inc., Chicago, IL, USA), version 17.0, and α level will be set at .05.

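### The regression meant to answer the primary SNP-by-exercise question lists neither the randomised arm nor any SNP-by-arm product, and its ten listed variables do not match the stated sample size of 140.

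*Protocol article*

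**What the plan says.** All references are to the protocol article.

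- **Objective (Background).** "the primary objective of this clinical trial is to investigate the existence of an interaction among TNF-α rs1800629, IL6 rs1800795, IL10 rs1800896" and the effect of exercise in older women.
- **Design (Recruitment of participants).** Participants are randomised to muscle strengthening (MSE) or aerobic exercise (AE). Both arms are active and there is no non-exercise control.
- **Purpose of the regression (Sample size).** It is "to explore the SNP influence on the effects of exercise on plasma levels of cytokines" and on physical performance.
- **Variables (Sample size).** "The explanatory variables are age, anthropometric measurements (Body Mass Index and Waist Circumference), physical activity level, presence of depression and stress levels". Stress is then specified as the Perceived Stress Scale and salivary cortisol, and the list ends with three SNPs, each coded in two groups.
- **Sample size.** The rule is given as "considering the sample calculation of (10 x (K + 1), where K is the number of explanatory variables of the model". The total drawn from it is 140 women.
- **Analysis (Statistical analyses).** "The multivariate linear regression analysis will be performed to explore the interaction and the effect of polymorphisms on the variables", these being cytokine levels and physical performance. The text does not say what the polymorphisms interact with, or whether the outcome is a level or a change. Between-group and within-group comparisons are assigned to an ANOVA for which no genotype factor is named.

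**The concern.** A question about whether genotype modifies an exercise effect needs an exercise term and its product with genotype. The only exercise factor that is randomised here is the arm. It is absent from the regression list, and genotype is absent from the description of the ANOVA. Neither analysis, as described, contains the contrast that the randomisation supports.

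Two things are at stake. A SNP coefficient from the listed model could be reported as a gene-by-exercise result when it is a non-randomised genotype association. And a real difference in genotype effect between the two exercise types could go unseen, because the listed model averages over it.

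**Working it through.** **1. Count the listed variables.** Age (1), Body Mass Index (2), waist circumference (3), physical activity level (4), depression (5), Perceived Stress Scale (6), salivary cortisol (7), and the TNF-α, IL-6 and IL-10 SNP indicators (8 to 10). So K = 10, with no arm and no product.

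**2. Try to reproduce 140.** The rule is N = 10 × (K + 1).
- Ten listed variables: 10 × 11 = 110.
- Working back from 140: K = 140/10 − 1 = 13, three more than are listed.
- Grouping related measures lowers the figure: K = 8 or 9 gives 90 or 100.
- Ten plus arm: 10 × 12 = 120.
- Ten plus three SNP-by-arm products without arm: 10 × 14 = 140. Three SNP-by-SNP products, or two dummies per SNP, also give 140, but the dummies contradict the stated two-group coding.
- Dropout inflation from 110 to 140 would need 1 − 110/140 = 21%. No dropout rate is stated.

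The stated figure therefore does not follow from the stated list, and several different additions would produce it.

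**3. What the listed model estimates.** Let a SNP have effect b1 on an outcome in the MSE arm and b2 in the AE arm. With equal allocation (assumed), a model without arm or product estimates about (b1 + b2)/2 for that SNP. The interaction is b1 − b2. These are different quantities, and one can be zero while the other is large.

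**4. Illustration under assumptions.** Take N = 140, 1:1 allocation, 30% of women in the SNP group, residual SD 1, b1 and b2 equal to 0.6 SD in opposite directions, and 2,000 simulated trials. The average is 0 and the interaction is 1.2 SD. A SNP-only model was significant in about 6% of runs. The product term was significant in about 89%. This is a deliberately extreme crossover case. It shows what can be missed, not what is likely.

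**5. What 140 could detect.** Assume 80% power, two-sided 0.05 (the article gives 0.05 without sidedness), residual SD 1 and a SNP-group share p. The detectable SNP-by-arm contrast is (1.96 + 0.84) × √[1/(140 × p(1 − p) × 0.25)].
- p = 50%: 0.95 SD
- p = 30%: 1.03 SD
- p = 15%: 1.33 SD

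For a pooled SNP main effect the factor 0.25 drops out and the values halve, to 0.47, 0.52 and 0.66 SD.

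**6. Scope.** The Abstract names six measured primary outcomes (sTNFR-1, sTNFR-2, IL-6, IL-10, Timed Up and Go, 10-Meter Walk). The Primary outcome measure section adds TNF-α. That gives 3 × 6 = 18 or 3 × 7 = 21 SNP-by-arm contrasts. This counts what is unspecified and does not measure bias.

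**7. N for a model that contains the contrast.**
- Ten listed + arm + three products: K = 14, N = 150.
- The same plus baseline value: K = 15, N = 160.
- Baseline, arm, three SNPs, three products, age and Body Mass Index: K = 10, N = 110.

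**The case against.** The strongest defence is that the list is incomplete prose, not the full model. The article's own 140 implies 13 variables, and three is exactly the number of SNP-by-exercise products. The article also uses physical activity as a term for the intervention, in the Abstract's aim and under Recruitment of participants. Since all entrants must be sedentary, a baseline activity covariate would vary little. If physical activity level means the arm, ten variables plus three products give 140 exactly. The Statistical analyses section does name an interaction, and a condensed article may leave the full equation to another document.

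Part of this stands. A reader might infer that the list is exhaustive and that the trial cannot test its primary interaction. The documents do not support that much, because the arithmetic shows that the list and N were not built from the same model. But the rescue is not stated anywhere. Physical activity level appears among participant characteristics and is never defined as the arm, and no product is named. SNP-by-SNP products fit the count equally well, and the Discussion stresses interaction between genotypes. Nor is this merely detail left out: the article states a variable list and bases N on its length.

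A second defence is that the outcome may be change from baseline, so that a SNP coefficient would describe genotype differences in response during training. A reader might otherwise infer that such a coefficient says nothing about exercise response. That is too strong, because the article does not define the outcome as level or change. Even as change, the coefficient would pool both arms, and without a non-exercise control it could not be separated from change that would have occurred anyway.

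**Conclusion.** The point holds as a mismatch between objective, listed model and sample size. As listed, the regression has ten terms and estimates SNP main effects pooled over arms. These are genotype associations with level or, if the outcome is change, genotype differences in pre-post change that cannot be attributed to exercise. None of the 18 to 21 SNP-by-arm contrasts is specified. The list gives 110, not 140, and 140 implies three unnamed variables.

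The conclusion rests on reading physical activity level as a participant characteristic. If it was meant as the arm, the products are still not listed.

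One limit applies to any repair. With two active arms, an arm-by-SNP term tests whether genotype modifies the difference between strengthening and aerobic exercise. That is narrower than the effect of exercise as such, which this design cannot isolate.

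**What to change.** In Sample size and Statistical analyses, state one model for each primary outcome: post-intervention value on baseline value, arm (MSE/AE), three SNP indicators, three arm-by-SNP products and a prespecified covariate set. Report the arm-by-SNP coefficients with 95% confidence intervals as the randomised test of whether genotype modifies the difference between the two exercise types. Label SNP main effects, and any pooled genotype differences in change, as non-randomised associations. Say whether physical activity level is a baseline covariate.

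Then restate K and N to match the final list. Keeping all ten variables with arm and three products gives 150, or 160 with baseline value. The reduced set with age and Body Mass Index gives 110, within the planned 140.

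No new measurements are needed, but there is a cost beyond wording. The reduced set drops waist circumference, physical activity level, depression, Perceived Stress Scale and salivary cortisol, and each needs a stated reason. If they are all kept at 140, the ten-per-variable rule is no longer met, and the article should say so.
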